**GUIDANCE ON ANSWERING QUESTIONS 4-6:**

**These questions must be completed by all applicants. You should note the following:**

**(i) If you have answered NO to question 2, may need to seek separate ethics approval from an NHS Research Ethics Committee for this study. The ISAC will provide advice on whether this may be needed.**

**(ii) If you have answered YES answered to question 2 above and you will be using data obtained from the GPRD Group at the MHRA, this study does not require separate ethics approval from an NHS Research Ethics Committee.**

**If you will be using data obtained from EPIC, you will need to consult the data provider regarding their arrangements for obtaining ethics approval for the study.**

**NB:** Answering YES to question 2 means that the answers to questions 7-9 should all be NO. If any of the answers below are YES please review your answer to question 2 as it should be NO.

| 1. Has this protocol been peer reviewed by another Committee?   Yes* No  ** Please state in your protocol the name of the reviewing Committee(s) and provide an outline of the review process and outcome.* |
| --- |
| 1. Does the study involve linking to patient *identifiable* data from other sources?   Yes No |
| 1. Does this study require contact with patients in order for them to complete a questionnaire?   Yes No |
| 1. Does this study require contact with patients in order to collect a sample?   Yes* No  ** Please state what will be collected* |
| 1. Type of Study *(please tick one box below)*   Adverse Drug Reaction Drug Use  Disease Epidemiology Pharmacoeconomic  Drug Effectiveness  Other |
| 1. Data source *(please tick one box below)*   GPRD, MHRA:  Sponsor has on-line access  Purchase of ad hoc dataset  Commissioned study  Other  *(please specify)* GPRD |
| 1. Financial Sponsor of study   Pharmaceutical Industry *(please specify)*        Academia*(please specify)*  Government / NHS *(please specify)*        None  Other *(please specify)* |
| 1. This study is intended for:   Publication in peer reviewed journals  Presentation at scientific conference  Presentation at company/institutional meetings  Other |
| 1. Principal Investigator (full name, job title, organisation & e-mail address for correspondence regarding this protocol)   [name], Research Statistician, GPRD, [contact] |
| 1. Affiliation (full address)   GPRD, MHRA, [name] |

**Protocol content checklist**

In order to help ensure that protocols submitted for review contain adequate information for protocol evaluation, ISAC have produced instructions on the content of protocols for research using GPRD data. These instructions are available on the GPRD website ([www.gprd.com/ISAC](http://www.gprd.com/ISAC)). All protocols using GPRD data which are submitted for review by ISAC must contain information on the areas detailed in the instructions. IF you do not feel that a specific area required by ISAC is relevant for your protocol, you will need to justify this decision to ISAC.

Applicants must complete the checklist below to confirm that the protocol being submitted includes all the areas required by ISAC, or to provide justification where a required area is not considered to be relevant for a specific protocol. Protocols will not be circulated to ISAC for review until the checklist has been completed by the applicant.

**Please note, your protocol will be returned to you if you do not complete this checklist, or if you answer ‘no’ and fail to include justification for the omission of any required area.**

|  | **Included in protocol?** | |  |
| --- | --- | --- | --- |
| **Required area** | **Yes** | **No** | **If no, reason for omission** |
| ***Lay Summary (max.200 words)*** |  |  |  |
| ***Background*** |  |  |  |
| ***Objective, specific aims and rationale*** |  |  |  |
| ***Study Type***  *Hypothesis Generating*  *Hypothesis Testing* |  |  | **This study is about data linkage, not hypotheses generation or testing** |
| ***Study Design*** |  |  | **As above** |
| ***Sample size/ power calculation***  ***(Please provide detailed justification of***  ***sample size in the protocol)*** |  |  | **As above** |
| ***Study population***  ***(including estimate of expected number of***  ***relevant patients in the GPRD)*** |  |  |  |
| ***Selection of comparison group(s) or controls*** |  |  |  |
| ***Exposures, outcomes and covariates*** |  |  |  |
| ***Data/ Statistical Analysis***  *Hypothesis Generating*  *Hypothesis Testing* |  |  | **As above** |
| ***Patient/ user group involvement †*** |  |  |  |
| ***Limitations of the study design, data sources***  ***and analytic methods*** |  |  |  |
| ***Plans for disseminating and communicating study results*** |  |  |  |

***† It is expected that many studies will benefit from the involvement of patient or user groups in their planning and refinement, and/or in the interpretation of the results and plans for further work. This is particularly, but not exclusively true of studies with interests in the impact on quality of life. Please indicate whether or not you intend to engage patients in any of the ways mentioned above.***

*ISAC strongly recommends that researchers using GPRD consider registering as a NRR data provider in order that others engaged in research within the UK can be made aware of current works. The* ***National Research Register (NRR)*** *is a register of ongoing and recently completed research projects funded by, or of interest to, the United Kingdom's National Health Service. Information on the NRR is available on* [*www.nrr.nhs.uk*](http://www.nrr.nhs.uk/) *.*

***Please Note: Registration with the NRR is entirely voluntary and will not replace information on ISAC approved protocols that are published in summary minutes or in the ISAC annual report****.*

**EXTENDING THE MOTHER BABY LINK**

**PROTOCOL**

**LAY SUMMARY**

The GPRD Mother Baby Link currently utilises information available within the database to identify mother and baby pairs. This allows researchers to study individuals within family units (e.g. whether taking a specified drug during pregnancy is associated with certain outcomes in the baby). However, there is the possibility to extend the scope from a mother to live baby link based purely on GPRD data, to a full pregnancy register incorporating data from HES and ONS mortality data.

**BACKGROUND**

The ability to study individuals within family units in epidemiology is very useful. As well as being able to look at familial aspects of disease, increased focus is being placed on the importance of in-utero exposures with respect to conditions manifested in the offspring. The best examples are studies into the teratogenic effects of drugs, which are hard to investigate using traditional pre-marking methodologies such as RCTs for obvious ethical reasons.

In GPRD there is a practice-specific family number that can be used to identify people within the same family. This is primarily based on residence, but can be edited in Vision where members of different families live at the same address. The existence of this variable allows us to link members of families together, and particularly mothers with their children. Furthermore, because both pregnancy and delivery information is recorded during the long follow up time within GPRD, it is possible to follow some children registered on GPRD from conception rather than from birth. This means the GPRD can be used to undertake the sort of studies that require information in all three trimesters.

To help users identify the linked mothers and children GPRD provide a Mother – Baby linked list. This list was first produced in 2004, extended in 2005, and was updated in 2010 to run using GPRD Gold data. The list is currently created on a monthly basis with new Read codes and entity types added. Now that the link is running efficiently on GPRD Gold data, there is the possibility to refine and extend the scope from a mother to live baby link based purely on GPRD data, to a full pregnancy register incorporating data from HES and ONS mortality data.

**OBJECTIVES, AIMS AND RATIONALE**

There are two main objectives of this study:

1. To refine the mother baby link, evaluating the opportunities brought by linked HES and ONS data.
2. To extend the mother baby link to a full pregnancy register including pregnancies resulting in termination, miscarriage and stillbirth.

**STUDY POPULATION**

Patients will be identified independently in the GPRD, HES and ONS data on the basis of dataset specific codes and variables related to pregnancy and its outcomes:

GPRD Read codes (clinical, referral and test files)

Entity types[[1]](#footnote-2) (clinical and test files)

Prescription exemption (patient file)

Consultation type (consultation file)

Referral specialism (referral file)

HES Episode type (delivery and birth files)

ICD codes

OPCS procedure codes

ONS ICD codes

The mother’s age at each estimated delivery date will be calculated as the difference between the year of the estimated delivery date and the mother’s birth year. Delivery records will be restricted to mothers between the ages of 12 and 49.

All GPRD registered acceptable patients born after 1986 will be considered for inclusion as children in the mother baby link.

Data will be utilised from the full time period available for each data source (i.e. 1987 to 2011 for GPRD, and 1997 to 2010 for HES/ONS) and across all practices (although HES/ONS data will only be available for practices consenting to take part in the linkage program, currently 224 in England).

The last monthly version of the existing Mother Baby Link (March 2011) included 615,661 mothers and 886,677 babies.

**EXPOSURES, OUTCOMES AND COVARIATES**

Pregnancy and pregnancy outcomes will be identified using the methods listed above. All women with at least one indication of pregnancy will be included in the pregnancy register. A Read code list of the existing codes for live birth is included as an appendix.

**DATA ANALYSIS**

All analyses will be conducted using Stata version 11.1. The following four stages of the project will be conducted.

Stage One

Linked HES data, including the information available in the delivery and birth HES data, but also standard HES data (including procedures and ICD codes), will be evaluated. The HES data will be seen, at this stage, as an additional data source for estimating the delivery date for the mother and the birth date for the baby. Additional information, where found, will be incorporated into the algorithm. The ease and efficiency of this process will be evaluated.

Stage Two

ONS mortality data will also be considered for potential dates of live births, although it is expected this will be utilised more in stage three of the study.

Stage Three

When the mother baby link is optimised for mothers and live births, the next stage will be to extend its remit to a full pregnancy register including pregnancies resulting in termination, miscarriage and stillbirth. This will require thorough and detailed searching of the data available in GPRD, HES and ONS. Methods to handle conflicting records will need to be established. The goal is a complete pregnancy history for each woman in GPRD, with details of pregnancy outcomes, estimated conception and delivery dates, and gestational age at birth.

Stage Four

A validation exercise will be undertaken once all information has been incorporated into the pregnancy register. This will involve searching the GPRD free text for evidence of pregnancies to establish the sensitivity and specificity of the mother baby link. Questionnaires will be sent to GPs to ask whether the match between the mother and baby is correct.

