**LIMITATIONS**

Many babies do not have birth month in their GPRD records (and date of birth is not available) making matching between mother and baby more challenging. All matching between mothers and babies will be based on probabilistic methods, although the validation exercise will give an indication of sensitivity and specificity. Data from HES and ONS is limited by geography, practice consent and data coverage period. There are known data quality issues with HES delivery and birth data, which may prevent full utilisation of this data source.

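### Objective 1 asks what HES and ONS data add to the mother baby link, but the protocol plans no comparison of accuracy with and without them

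*Protocol*

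**What the plan says.** The first objective (Objectives, Aims and Rationale) is "To refine the mother baby link, evaluating the opportunities brought by linked HES and ONS data".

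The Data Analysis section sets the order of work:

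- **Stage One** opens with a general statement that the HES files will be assessed, without saying against what. HES is treated as "an additional data source for estimating the delivery date for the mother and the birth date for the baby". Then: "Additional information, where found, will be incorporated into the algorithm. The ease and efficiency of this process will be evaluated". The second of these two sentences holds the one criterion named.
- **Stage Two** says ONS mortality data will be considered for live-birth dates. No criterion is given.
- **Stage Three** starts once the live-birth link is regarded as optimised, and leaves the handling of conflicting records to be worked out.
- **Stage Four** is the only check of accuracy: "A validation exercise will be undertaken once all information has been incorporated into the pregnancy register". It consists of "searching the GPRD free text for evidence of pregnancies to establish the sensitivity and specificity of the mother baby link", plus questionnaires asking GPs whether a mother and baby are correctly matched.

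The Limitations section adds: "There are known data quality issues with HES delivery and birth data, which may prevent full utilisation of this data source".

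**The concern.** To know what a new data source does to a linkage, one needs the accuracy of the link with it and without it, on the same people. The protocol measures accuracy once, on the merged product. An ease-and-efficiency criterion describes the work of adding HES, not whether links or dates become more often correct.

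The protocol itself warns about the quality of the HES delivery and birth files, the same files that are to supply dates. If HES information introduces errors, nothing in the four stages is designed to show it. A larger count of pairs after the merge would not settle the matter either, because a count does not separate correct additions from wrong ones. Users would receive a register without knowing whether the part informed by HES/ONS is better or worse than the GPRD-only link that they already have.

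**Working it through.** The protocol gives no accuracy figure, target or sample size for validation, so there is nothing to reproduce. The check sets the sections side by side and adds one piece of arithmetic.

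**1. Is there a before-and-after measurement?** Let A0 be the accuracy of the GPRD-only link and A1 that of the merged link, on the same patients. The quantity behind Objective 1 is A1 − A0. Stage Four estimates something like A1. No stage estimates A0. One measured quantity cannot yield a difference of two.

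**2. Could an existing figure stand in for A0?**

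- *The March 2011 link.* Study Population gives its size (615,661 mothers and 886,677 babies) but no accuracy. The Background says the list is rebuilt monthly with new codes and entity types. A later comparison would therefore mix the effect of HES with code-list changes and newly accrued births.
- *Practices without HES/ONS.* Limitations says availability depends on geography, practice consent and coverage period. These are different patients in different places.

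Neither gives a comparison on the same patients.

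**3. Does the validation address what HES is used for?** Stage One brings HES in to estimate the mother's delivery date and the baby's birth date. Stage Four checks (a) evidence of pregnancy in free text and (b) correctness of the match. A pair can be matched correctly and still carry a wrong date. Date accuracy is not checked at any stage.

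**4. Could Stage Four be split by source afterwards?** Only partly. If the source of each link is stored, added and changed pairs can be identified. Pairs that were in the GPRD-only link but dropped out after HES was added are not in the merged register and cannot be sampled from it. The net change in correct pairs is

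N_added × a_added + N_changed × (a_new − a_old) − N_lost × a_lost,

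where each a is the proportion correct in that group. The last term, and a_old for changed pairs, need the GPRD-only output.

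**5. What does pooling do?** Study Population gives GPRD data for 1987-2011 and HES/ONS data for 1997-2010:

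- GPRD: 2011 − 1987 + 1 = 25 calendar years
- HES/ONS: 2010 − 1997 + 1 = 14 calendar years
- 14 / 25 = 0.56, or 56%

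Within those years only the consenting practices (224, in England) can be affected. If s is the share of pairs in linked practices and years, and d is the change in accuracy there, the pooled change is s × d, smaller than d whenever s is below 1. The value of s cannot be computed: the total number of practices is not given, and the 56% counts calendar years, not pairs. The direction of the dilution is certain; its size is not.

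**The case against.** The strongest reply is that the objective is not an accuracy hypothesis. It speaks of opportunities, and the protocol checklist says the study is about linkage rather than generating or testing hypotheses. Counts of added dates or links would answer part of it. Patients are to be identified independently in each source, so a cross-source comparison remains feasible, and nothing forbids reporting Stage Four by source, practice or year. Overlap tables and sampling strata are also often left to an analysis plan, which may exist but is not shown.

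Much of this stands, and it rules out three stronger readings that a reader might infer:

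- *That Objective 1 cannot be answered.* The documents do not support this. The comparison is missing from the plan, not impossible, and the part of the objective that concerns availability and volume can be met.
- *That HES is to be judged on ease and efficiency alone.* Stage One also says, in general terms, that the HES data will be evaluated. Ease and efficiency is the only criterion named, which is a narrower statement.
- *That HES will override GPRD unconditionally.* No override rule is stated. HES is described as additional, Limitations allows that quality problems may restrict its use, and conflict handling is left open in Stage Three.

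What does not fall away is the sequence. The protocol itself, not a later plan, places its only accuracy check after all sources are in, and Limitations gives no rule that turns the quality warning into a decision about when to use HES. Splitting Stage Four afterwards would still miss lost pairs and dates. Dilution applies only to a pooled figure and disappears if results are restricted to linked practices and years, but the protocol plans no such restriction.

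**Conclusion.** The concern holds in this form: Objective 1 includes evaluating HES and ONS, yet the protocol plans no comparison of link or date accuracy with and without them. Followed as written, it yields one post-merge sensitivity and specificity and a questionnaire result on matches, and these cannot show whether HES/ONS improved, left unchanged or worsened the link. The dates that HES is meant to help estimate are not validated at all.

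The only size the documents support is that HES/ONS can reach at most 14 of 25 calendar years (56%), and within those only the consenting practices. Any figure for the diluted effect would need an assumed share of practices and an assumed gain in accuracy, and the protocol supplies neither. The conclusion rests on the wording of the objective, the four stages and the limitations. It does not assume that HES data are in fact harmful. This should be corrected before Stage One starts, because the GPRD-only result has to be kept from that point.

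**What to change.** 1. Freeze the GPRD-only algorithm and retain its output as the comparator.
2. In the consenting practices and for 1997-2010 only, run GPRD-only and GPRD+HES (and +ONS) on the same patients.
3. Before HES is allowed to replace any GPRD information, tabulate pairs as unchanged, gained, lost or changed, and the distribution of the difference in days between GPRD-estimated and HES dates. Date differences show agreement, not which source is right, so large disagreements should mark categories where replacement needs further support.
4. Draw the Stage Four GP questionnaires, already planned, in four strata: unchanged, added, changed and lost. Sample the lost stratum from the retained GPRD-only output. For changed pairs, ask about both versions of the match.
5. Report accuracy by stratum, and obtain the overall figure for the merged link by weighting the unchanged, added and changed strata by their share of its pairs.

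The cost is some extra analysis and storage of one additional output. With a fixed number of questionnaires, fewer fall on unchanged pairs, so the overall figure must be reweighted and will be somewhat less precise for that group.

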**USER GROUP INVOLVEMENT**

The key users of the Mother Baby Link will be GPRD users. As such, a number of academic groups with an interest in maternity data have reviewed this protocol and will be active collaborators on the study, especially in the areas of interpretation and plans for future work.

**LIMITATIONS**

Many babies do not have birth month in their GPRD records (and date of birth is not available) making matching between mother and baby more challenging. All matching between mothers and babies will be based on probabilistic methods, although the validation exercise will give an indication of sensitivity and specificity. Data from HES and ONS is limited by geography, practice consent and data coverage period. There are known data quality issues with HES delivery and birth data, which may prevent full utilisation of this data source.

**DISSEMINATION OF RESULTS**

The results of this study will be communicated to GPRD users and license holders. Findings will also be published for peer review in international scientific journals and conferences as appropriate.

It should be noted that all delivery dates will be estimated based upon probabilistic linkage, and GPRD will never release information as to whether a delivery date is a confirmed date of birth or not.

READ CODES FOR LIVE BIRTHS

| Read Code | Read Term |
| --- | --- |
| 6311 | Home birth |
| 6312 | GP unit birth |
| 6313 | Consultant unit birth |
| 6314 | Nursing home birth |
| 6315 | Ambulance birth |
| 6316 | Born before arrival |
| 6321 | 1st stage of labour length |
| 6322 | 2nd stage of labour length |
| 6323 | 3rd stage of labour length |
| 6331 | Single live birth |
| 6333 | Twins - both live born |
| 6334 | Twins - 1 still + 1 live born |
| 6335 | Twins - both still born |
| 6336 | Triplets - all live born |
| 6337 | Triplets -2 live+ 1 still born |
| 6341 | Baby male |
| 6342 | Baby female |
| 6343 | 2 male babies |
| 6344 | 2 female babies |
| 6345 | 1 male + 1 female baby |
| 6346 | 3 male babies |
| 6347 | 2 male + 1 female babies |
| 6348 | 1 male + 2 female babies |
| 6349 | 3 female babies |
| 6351 | Baby premature 36-38 weeks |
| 6352 | Baby v. premature 32-36 weeks |
| 6353 | Baby extremely prem.28-32 week |
| 6354 | Baby full term maturity |
| 6355 | Baby post-mature |
| 6356 | Baby premature 26-28 weeks |
| 6357 | Baby premature 24-26 weeks |
| 6358 | Baby premature 39 weeks |
| 6359 | Baby premature 38 weeks |
| 6361 | Baby BW = < 3% (under 2500g) |
| 6362 | Baby BW = 3% - 9% (2500-2849g) |
| 6363 | Baby BW = 10%-24% (2850-3149g) |
| 6364 | Baby BW = 25%-49% (3150-3449g) |
| 6365 | Baby BW = 50%-74% (3450-3749g) |
| 6366 | Baby BW = 75%-89% (3750-4049g) |
| 6367 | Baby BW = 90%-96% (4050-4399g) |
| 6368 | Baby BW = > 96% (over 4499g) |
| 6369 | Baby BW = 4400 - 4499g |
| 6371 | Birth HC = < 3rd centile |
| 6372 | Birth HC = 3rd-9th centile |
| 6373 | Birth HC = 10th-24th centile |
| 6374 | Birth HC = 25th-49th centile |
| 6375 | Birth HC = 50th-74th centile |
| 6376 | Birth HC = 75th-89th centile |
| 6377 | Birth HC = 90th-96th centile |
| 6378 | Birth HC = > 97th centile |
| 6381 | Birth length = < 3rd centile |
| 6382 | Birth length=3rd-9th centile |
| 6383 | Birth length=10th-24th centile |
| 6384 | Birth length=25th-49th centile |
| 6385 | Birth length=50th-74th centile |
| 6386 | Birth length=75th-89th centile |
| 6391 | Apgar at 1 minute = 0 |
| 6392 | Apgar at 1 minute = 1 |
| 6393 | Apgar at 1 minute = 2 |
| 6394 | Apgar at 1 minute = 3 |
| 6395 | Apgar at 1 minute = 4 |
| 6396 | Apgar at 1 minute = 5 |
| 6397 | Apgar at 1 minute = 6 |
| 6398 | Apgar at 1 minute = 7 |
| 6399 | Apgar at 1 minute = 8 |
| 6411 | Bottle fed at 10 days |
| 6412 | Breast fed at 10 days |
| 6413 | Breast + supp. fed at 10 days |
| 6421 | Bottle fed at 6 weeks |
| 6422 | Breast fed at 6 weeks |
| 6423 | Breast fed + supp. at 6 weeks |
| 6424 | On solids at 6 weeks |
| 6431 | Bottle fed at 3 months |
| 6432 | Breast fed at 3 months |
| 6433 | Breast + supp.fed at 3 months |
| 6434 | On solids at 3 months |
| 6441 | Bottle fed at 6 months |
| 6442 | Breast fed at 6 months |
| 6443 | Breast + supp. fed at 6 months |
| 6444 | On solids at 6 months |
| 6445 | On normal diet at 6 months |
| 1Y1..00 | Well baby |
| 62P..00 | Infant feeding method |
| 62P1.00 | Breast fed |
| 62P1.11 | Infant breast fed |
| 62P2.00 | Bottle fed |
| 62P2.11 | Infant bottle fed |
| 62P3.00 | Breast feeding with supplement |
| 62P4.00 | Breast changed to bottle feed |
| 62P5.00 | Breast feeding started |
| 62P6.00 | Breast feeding stopped |
| 62P7.00 | Bottle feeding started |
| 62P8.00 | Bottle feeding stopped |
| 62P9.00 | Infant weaned |
| 62PA.00 | Mother currently breast feeding |
| 62PB.00 | Bottle changed to breast |
| 62PC.00 | Breast feeding problem |
| 62PD.00 | Lactation established |
| 62PZ.00 | Infant feeding method NOS |
| 62Q..00 | Postnatal care provider |
| 62Q1.00 | P/N care from consultant |
| 62Q2.00 | P/N care from G.P. |
| 62Q3.00 | P/N - shared care |
| 62Q4.00 | No post natal care |
| 62Q5.00 | P/N care refused |
| 62Q6.00 | Postnatal care |
| 62QZ.00 | Post natal care NOS |
| 62R..00 | Postnatal visits |
| 62R1.00 | P/N - first day visit |
| 62R2.00 | P/N - second day visit |
| 62R3.00 | P/N - third day visit |
| 62R4.00 | P/N - fourth day visit |
| 62R5.00 | P/N - fifth day visit |
| 62R6.00 | P/N - sixth day visit |
| 62R7.00 | P/N - seventh day visit |
| 62R8.00 | P/N - eighth day visit |
| 62R9.00 | P/N - ninth day visit |
| 62RA.00 | P/N - tenth day visit |
| 62RB.00 | P/N care started at birth |
| 62RC.00 | P/N care <48hrs after birth |
| 62RD.00 | P/N care >48hrs after birth |
| 62RZ.00 | Postnatal visit NOS |
| 62S..00 | Maternal P/N 6 week exam. |
| 62S..11 | Postnatal exam. - maternal |
| 62S1.00 | Maternal P/N exam. not offered |
| 62S2.00 | Maternal P/N exam. offered |
| 62S3.00 | Maternal P/N exam. refused |
| 62S4.00 | Maternal P/N exam. defaulted |
| 62S5.00 | Maternal P/N exam. done |
| 62S6.00 | Postnatal examination minor problem found |
| 62S7.00 | Postnatal examination normal |
| 62SZ.00 | Maternal P/N 6 week exam. NOS |
| 62T..00 | Misc. postnatal data |
| 62T1.00 | Puerperal depression |
| 62TZ.00 | Misc. post natal data NOS |
| 62X4.00 | Length of gestation at birth |
| 63...00 | Birth details |
| 631..00 | Place of birth |
| 631..11 | Born - place delivered |
| 631Z.00 | Place of birth NOS |
| 632..00 | Length of labour |
| 632Z.00 | Length of labour NOS |
| 633..00 | Outcome of delivery |
| 633..11 | Livebirth |
| 633..13 | Triplet birth |
| 633..14 | Twin birth |
| 633a.00 | Birth of child |
| 633Z.00 | Outcome of delivery NOS |
| 634..00 | Sex of baby |
| 634..11 | Delivery - sex of baby |
| 634..12 | Female baby |
| 634..13 | Male baby |
| 634Z.00 | Sex of baby NOS |
| 635..00 | Maturity of baby |
| 635..11 | Full term baby |
| 635..12 | Postmature baby |
| 635..13 | Premature baby |
| 635A.00 | Baby premature 37 weeks |
| 635B.00 | Baby premature 36 weeks |
| 635Z.00 | Baby maturity NOS |
| 636..00 | Birthweight of baby |
| 636..11 | Birthweight |
| 636..12 | Weight - baby |
| 636A.00 | Baby BW = below 751gm |
| 636B.00 | Baby BW = 751g-1kg |
| 636C.00 | Baby BW = 1.0-1.5kg |
| 636D.00 | Baby BW = 1.5-2.0kg |
| 636E.00 | Baby BW = 2.0 - 2.5kg |
| 636F.00 | Baby BW = above 2.5kg |
| 636Z.00 | Birthweight of baby NOS |
| 637..00 | Birth head circumference |
| 637Z.00 | Birth head circumference NOS |
| 638..00 | Birth length |
| 638Z.00 | Birth length = > 97th centile |
| 639..00 | Apgar at 1 minute |
| 639A.00 | Apgar at 1 minute = 9 |
| 639B.00 | Apgar at 1 minute = 10 |
| 639Z.00 | Apgar at 1 minute NOS |
| 63A..00 | Apgar at 5 minutes |
| 63A1.00 | Apgar at 5 minutes = 0 |
| 63A2.00 | Apgar at 5 minutes = 1 |
| 63A3.00 | Apgar at 5 minutes = 2 |
| 63A4.00 | Apgar at 5 minutes = 3 |
| 63A5.00 | Apgar at 5 minutes = 4 |
| 63A6.00 | Apgar at 5 minutes = 5 |
| 63A7.00 | Apgar at 5 minutes = 6 |
| 63A8.00 | Apgar at 5 minutes = 7 |
| 63A9.00 | Apgar at 5 minutes = 8 |
| 63AA.00 | Apgar at 5 minutes = 9 |
| 63AB.00 | Apgar at 5 minutes = 10 |
| 63AZ.00 | Apgar at 5 minutes NOS |
| 63B..00 | Apgar at 10 minutes |
| 63B1.00 | Apgar at 10 minutes = 0 |
| 63B2.00 | Apgar at 10 minutes = 1 |
| 63B3.00 | Apgar at 10 minutes = 2 |
| 63B4.00 | Apgar at 10 minutes = 3 |
| 63B5.00 | Apgar at 10 minutes = 4 |
| 63B6.00 | Apgar at 10 minutes = 5 |
| 63B7.00 | Apgar at 10 minutes = 6 |
| 63B8.00 | Apgar at 10 minutes = 7 |
| 63B9.00 | Apgar at 10 minutes = 8 |
| 63BA.00 | Apgar at 10 minutes = 9 |
| 63BB.00 | Apgar at 10 minutes = 10 |
| 63BZ.00 | Apgar at 10 minutes NOS |
| 63C..00 | Baby misc. ""at-risk"" factors |
| 63C1.00 | Risk factor - been on SCBU |
| 63C1.11 | Risk factor - been on special care unit |
| 63C2.00 | Bonding problems |
| 63C3.00 | Cot death liability |
| 63C4.00 | Battered baby suspect - FH |
| 63C5.00 | Maternal tobacco abuse |
| 63C6.00 | Maternal drug abuse |
| 63C7.00 | Maternal alcohol abuse |
| 63C8.00 | Mother < 20 years old |
| 63C9.00 | Mother has a social worker |
| 63CA.00 | H.V.: mother not managing well |
| 63CB.00 | Risk of non-accidental injury |
| 63CC.00 | Difficult to establish feeding |
| 63CD.00 | High risk infant |
| 63CE.00 | One of twins |
| 63CE.11 | Fraternal twin |
| 63CE.12 | Heterozygous twin |
| 63CE.13 | Identical twin |
| 63CE.14 | Monozygous twin |
| 63CF.00 | One of triplets |
| 63CZ.00 | Baby ""at-risk"" factors NOS |
| 63D..00 | Placental details |
| 63D1.00 | Placental weight |
| 63D2.00 | Placenta normal O/E |
| 63D3.00 | Placenta diameter |
| 63D4.00 | Placental infarct |
| 63D5.00 | Placental abnormality |
| 63D6.00 | Placenta incomplete |
| 63DZ.00 | Placental details NOS |
| 63E..00 | Labour details |
| 63E1.00 | Spontaneous onset of labour |
| 63E2.00 | Normal birth |
| 63E3.00 | Normal labour |
| 63F..00 | Birth details not known |
| 63Z..00 | Birth details NOS |
| 63Z..11 | Apgar normal |
| 641..00 | Infant feeding - at 10 days |
| 641Z.00 | Infant feeding at 10 days NOS |
| 642..00 | Infant feeding at 6 weeks |
| 642Z.00 | Infant feeding at 6 weeks NOS |
| 643..00 | Infant feeding at 3 months |
| 643Z.00 | Infant feeding at 3 months NOS |
| 644..00 | Infant feeding at 6 months |
| 644Z.00 | Infant feeding at 6 months NOS |
| 64a..00 | Child 8 week exam |
| 64a1.00 | Child 8 week exam. not offered |
| 64a2.00 | Child 8 week exam. not wanted |
| 64a3.00 | Child 8 week exam.not attended |
| 64a4.00 | Child 8 week exam. normal |
| 64a5.00 | 8 week exam.abnormal -for obs. |
| 64a6.00 | 8 week exam.abnormal -referred |
| 64a7.00 | 8 week exam.abn.-on treatment |
| 64B..00 | Child exam. - birth |
| 64B1.00 | Child not examined at birth |
| 64B2.00 | Child birth exam. - normal |
| 64B2.11 | Baby normal at birth |
| 64B3.00 | Birth exam. abnormal -for obs. |
| 64B4.00 | Birth exam. abnormal -referred |
| 64B5.00 | Birth exam abn. - on treatment |
| 64BZ.00 | Child exam. - birth NOS |
| 64C..00 | Child exam. - 10 day |
| 64C1.00 | Child not examined at 10 days |
| 64C2.00 | Child 10 day exam. - normal |
| 64C3.00 | 10 day exam.abnormal -for obs. |
| 64C4.00 | 10 day exam. abnormal-referred |
| 64CZ.00 | Child 10 day exam. NOS |
| 64D..00 | Child 6 week exam. |
| 64D1.00 | Child 6 week exam. not offered |
| 64D2.00 | Child 6 week exam. not wanted |
| 64D3.00 | Child 6 week exam.not attended |
| 64D4.00 | Child 6 week exam. normal |
| 64D5.00 | 6 week exam.abnormal -for obs. |
| 64D6.00 | 6 week exam.abnormal -referred |
| 64D7.00 | 6 week exam.abn.-on treatment |
| 64DZ.00 | Child 6 week exam. NOS |
| 64e..00 | Infant feeding at birth |
| 64e0.00 | Bottle fed at birth |
| 64e1.00 | Breast fed at birth |
| 64f..00 | Infant feeding at 4 months |
| 64f0.00 | Breast fed at 4 months |
| 64T1.00 | Child 3 month examination |
| 64T2.00 | Child 6 month examination NEC |
| 64V..00 | Child 6 month examination |
| 64V4.00 | Child 6 month exam normal |
| 64V5.00 | Child 6/12 exam abnorm for obs |
| 64V6.00 | Child 6/12 exam abnorm: refer |
| 64VZ.00 | Child 6/12 exam NOS |
| 67C..00 | Postnatal support group |
| 7F...11 | Childbirth operations |
| 7F...13 | Puerperium operations |
| 7F1..00 | Induction and delivery operations |
| 7F1..11 | Labour operations |
| 7F10.00 | Surgical induction of labour |
| 7F10000 | Fore water rupture of amniotic membrane |
| 7F10100 | Hind water rupture of amniotic membrane |
| 7F10y00 | Other specified surgical induction of labour |
| 7F10z00 | Surgical induction of labour NOS |
| 7F10z11 | Artificial rupture of membranes |
| 7F10z12 | ARM |
| 7F11.00 | Other induction of labour |
| 7F11000 | Oxytocic induction of labour |
| 7F11100 | Induction of labour using prostaglandins |
| 7F11200 | Syntocinon induction of labour |
| 7F11300 | Medical induction of labour |
| 7F11y00 | Other specified other induction of labour |
| 7F11z00 | Other induction of labour NOS |
| 7F12.00 | Elective caesarean delivery |
| 7F12000 | Elective upper uterine segment caesarean delivery |
| 7F12100 | Elective lower uterine segment caesarean delivery |
| 7F12111 | Elective lower uterine segment caesarean section (LSCS) |
| 7F12y00 | Other specified elective caesarean delivery |
| 7F12z00 | Elective caesarean delivery NOS |
| 7F13.00 | Other caesarean delivery |
| 7F13000 | Upper uterine segment caesarean delivery NEC |
| 7F13100 | Lower uterine segment caesarean delivery NEC |
| 7F13111 | Lower uterine segment caesarean section (LSCS) NEC |
| 7F13200 | Extraperitoneal caesarean section |
| 7F13300 | Emergency caesarean section |
| 7F13y00 | Other specified other caesarean delivery |
| 7F13z00 | Other caesarean delivery NOS |
| 7F14.00 | Breech extraction delivery |
| 7F14100 | Forceps to aftercoming head (breech) |
| 7F14y00 | Other specified breech extraction delivery |
| 7F14z00 | Breech extraction delivery NOS |
| 7F15.00 | Other breech delivery |
| 7F15000 | Spontaneous breech delivery |
| 7F15100 | Assisted breech delivery |
| 7F15y00 | Other specified other breech delivery |
| 7F15z00 | Other breech delivery NOS |
| 7F16.00 | Forceps cephalic delivery |
| 7F16000 | High forceps cephalic delivery with rotation |
| 7F16100 | High forceps cephalic delivery NEC |
| 7F16200 | Mid forceps cephalic delivery with rotation |
| 7F16300 | Mid forceps cephalic delivery NEC |
| 7F16400 | Low forceps cephalic delivery |
| 7F16500 | Trial of forceps delivery |
| 7F16600 | Failed forceps delivery |
| 7F16700 | Barton forceps cephalic delivery with rotation |
| 7F16900 | Kielland forceps cephalic delivery with rotation |
| 7F16y00 | Other specified forceps cephalic delivery |
| 7F16z00 | Forceps cephalic delivery NOS |
| 7F17.00 | Vacuum delivery |
| 7F17.11 | Ventouse delivery |
| 7F17.12 | Ventouse extraction |
| 7F17100 | Low vacuum delivery |
| 7F17200 | Vacuum delivery before full dilation of cervix |
| 7F17300 | Trial of vacuum delivery |
| 7F17y00 | Other specified vacuum delivery |
| 7F17z00 | Vacuum delivery NOS |
| 7F18.00 | Cephalic vaginal deliv abnorm presentation head - no instrum |
| 7F18000 | Manip cephalic vaginal deliv abnorm pres head without instrm |
| 7F18100 | Nonmanip cephal vagin deliv abnorm pres head without instrum |
| 7F18y00 | Cephalic vagin deliv abnorm pres head without instrument OS |
| 7F18z00 | Cephalic vagin deliv abnorm pres head without instrument NOS |
| 7F19.00 | Normal delivery |
| 7F19000 | Manually assisted vaginal delivery |
| 7F19100 | Water birth delivery |
| 7F19y00 | Other specified normal delivery |
| 7F19z00 | Normal delivery NOS |
| 7F1A.00 | Other methods of delivery |
| 7F1A000 | Caesarean hysterectomy |
| 7F1A200 | Cleidotomy of fetus to facilitate delivery |
| 7F1A300 | Drainage of hydrocephalus of fetus to facilitate delivery |
| 7F1A400 | Trial of labour NEC |
| 7F1Ay00 | Other specified other method of delivery |
| 7F1Az00 | Other method of delivery NOS |
| 7F1B.00 | Other operations to facilitate delivery |
| 7F1B000 | Episiotomy to facilitate delivery |
| 7F1B100 | Symphysiotomy to facilitate delivery |
| 7F1B300 | Manual dilatation of cervix |
| 7F1B400 | Incision of cervix to facilitate delivery |
| 7F1Bz00 | Other operation to facilitate delivery NOS |
| 7F1y.00 | Other specified induction or delivery operations |
| 7F1z.00 | Induction and delivery operations NOS |
| 7F23.00 | Immediate repair of obstetric laceration |
| 7F23.11 | Immediate repair of obstetric tear |
| 7F23.12 | Immediate suture of obstetric laceration |
| 7F23000 | Immed repair obstetric laceration of uterus or cervix uteri |
| 7F23100 | Immed repair obstetric laceration perineum & anal sphincter |
| 7F23200 | Immed repair obstetric laceration vagina and floor of pelvis |
| 7F23300 | Immediate repair of minor obstetric laceration |
| 7F23400 | Repair of episiotomy |
| 7F23500 | Repair of ruptured uterus |
| 7F23y00 | Other specified immediate repair of obstetric laceration |
| 7F23z00 | Immediate repair of obstetric laceration NOS |
| 7F25.13 | Monitoring during labour |
| 7F25100 | Fetal heart monitoring in labour |
| 8HE7.00 | Discharged from hospital within 6 hours of delivery |
| 8Hl8.00 | Referral to breast feeding peer support service |
| L100100 | Threatened abortion - delivered |
| L10z100 | Early pregnancy haemorrhage NOS - delivered |
| L110100 | Placenta praevia without haemorrhage - delivered |
| L111100 | Placenta praevia with haemorrhage - delivered |
| L112100 | Placental abruption - delivered |
| L114100 | Antepartum haemorrhage with trauma - delivered |
| L115100 | Antepartum haemorrhage with uterine leiomyoma - delivered |
| L11y100 | Other antepartum haemorrhage - delivered |
| L11z100 | Antepartum haemorrhage NOS - delivered |
| L120100 | Benign essential hypertension in preg/childb/puerp - deliv |
| L120200 | Benign ess hypert in preg/childb/puerp - deliv with p/n comp |
| L120400 | Benign essential hypertension in preg/childb/puerp +p/n comp |
| L121100 | Renal hypertension in pregnancy/childbirth/puerp - delivered |
| L122100 | Other pre-existing hypertension in preg/childb/puerp - deliv |
| L123100 | Transient hypertension of pregnancy - delivered |
| L123200 | Transient hypertension of pregnancy - deliv with p/n comp |
| L123400 | Transient hypertension of pregnancy + postnatal complication |
